# A multicenter open-label phase II trial to evaluate nivolumab and ipilimumab for 2nd line therapy in elderly patients with advanced esophageal squamous cell cancer (RAMONA)

**DOI:** 10.1186/s12885-019-5446-2

**Published:** 2019-03-14

**Keywords:** Esophageal squamous cell cancer, Elderly, Comprehensive geriatric assessment, Checkpoint inhibitors, Personalized medicine, Geriatric oncology

## Abstract

**Background:**

Advanced esophageal squamous cell cancer (ESCC) is frequently diagnosed in elderly patients. The impact of 2nd line chemotherapy is poorly defined. Recent data demonstrated effectiveness of checkpoint inhibitors in different squamous cell carcinomas. Therefore, we assess combined nivolumab/ipilimumab as 2nd line therapy in elderly ESCC patients.

**Methods:**

RAMONA is a multicenter open-label phase II trial. The primary objective is to demonstrate a significant survival benefit of nivolumab/ipilimumab in advanced ESCC compared to historical data of standard chemotherapy. Primary endpoint is therefore overall survival (OS). Major secondary objective is the evaluation of tolerability. Time to QoL deterioration will thus be determined as key secondary endpoint. Further secondary endpoints are tumor response, PFS and safety. We aim to recruit a total of *n* = 75 subjects that have to be > 65 years old. Eligibility is determined by the geriatric status (G8 screening and Deficit Accumulation Frailty Index (DAFI)). A safety assessment will be performed after a 3 cycle run-in phase of nivolumab (240 mg Q2W) to justify escalation for eligible patients to combined nivolumab (240 mg Q2W) and ipilimumab (1 mg/kg Q6W), while the other patients will remain on nivolumab only. RAMONA also includes translational research sub-studies to identify predictive biomarkers, including PD-1 and PD-L1 evaluation at different time points, establishment of organoid cultures and microbiome analyses for response prediction.

**Discussion:**

The RAMONA trial aims to implement checkpoint inhibitors for elderly patients with advanced ESCC as second line therapy. Novel biomarkers for checkpoint-inhibitor response are analyzed in extensive translational sub-studies.

**Trial registration:**

EudraCT Number: 2017–002056-86; NCT03416244, registered: 31.1.2018.

**Electronic supplementary material:**

The online version of this article (10.1186/s12885-019-5446-2) contains supplementary material, which is available to authorized users.

## Background

ESCC is the sixth leading cause of cancer-related death worldwide [1]. The disease is frequently diagnosed in advanced tumor stages and in elderly patients [1, 2].

Efficacy of chemotherapy in advanced ESCC is still poorly defined. While most patients undergo chemotherapy and/or chemo-radiation in first line according to the CROSS protocol using Paclitaxel and Carboplatin, effectiveness of second-line chemotherapy is discouraging [3, 4]. However, very recently Kojima et al. reported that pembrolizumab significantly improved OS compared to chemotherapy (paclitaxel, docetaxel or irinotecan) in patients with advanced esophageal or esophagogastric junction carcinoma whose tumors express PD-L1 (Combined Positive Score [CPS] ≥10, regardless of histology) (median 9.3 vs 6.7 mo; HR 0.69; 95% CI 0.52–0.93; *P* = 0.0074). OS at 12 months was 43% vs 20%, respectively. (KEYNOTE 181) [5].

Immunotherapy with antibodies against immune checkpoints like PD-1/PD-L1 represents a new treatment opportunity with relatively little side effects and first promising results in the treatment of squamous cell carcinoma patients [6–8]. With respect to esophageal cancer, preliminary results from an Asian study indicate efficacy of nivolumab [9]. From 64 heavily pre-treated patients, 11 (17, 95% CI 10–28) had an objective response and 16 (25, 95% CI 16–37) demonstrated stable disease. The median overall survival was 10.8 months (IQR 4.9–14.3) in this trial population (unselected for PD-L1 expression status). Long-term survival was also improved by pembrolizumab as described by Doi et al. [10].

Furthermore, the CheckMate 012 trial demonstrated that overall response rates could be doubled when PD-1 inhibitor nivolumab was combined with CTLA-4-inhibitor ipilimumab in advanced NSCLC patients [11]. In this trial, grade 3 and 4 adverse events were reported to occur in 33% of the patients treated with the combination therapy (nivolumab 3 mg/kg Q2W and ipilimumab 1 mg/kg Q6W). In the checkmate 032 in turn (nivolumab 3 mg/kg Q2W and ipilimumab 1 mg/kg Q3W), treatment related adverse events of grade 3 and 4 were only slightly enhanced when compared to nivolumab monotherapy (13% vs. 19%) [12].

There is an increasing need for improved treatment strategies for elderly ESCC patients. These strategies have to acknowledge the challenges of functional limitations and comorbidities in this increasing population. With increasing age, elderly patients develop chronic diseases and different comorbidities that may affect person’s capabilities, functional reserve and life expectancy [13]. However, assessment of these characteristics in the elderly population is time-consuming, therefore new assessment and screening tools are being developed. The poor knowledge of the role of chemotherapy and immunotherapy in these individuals, due to lack of enrolment of these patients in clinical trials, demands for novel concepts of clinical trials specifically designed for elderly patients.

With the RAMONA trial, we aim to address this high medical need by assessing nivolumab and ipilimumab in combination as second-line therapy of advanced ESCC in the elderly population. Patient eligibility will be assessed by geriatric screening tools in this trial. Moreover, we aim to establish novel biomarkers for checkpoint inhibition by extensive translational sub-studies.

## Methods/design

### Study design

RAMONA is a multicenter open-label phase II trial conducted in 34 centers in Germany (for overviews please refer to Additional file 1: Table S1). Key inclusion criteria areage ≥ 65 years at time of recruitmenthistologically approved diagnosis of advanced ESCCprogression after front line treatment (including chemo-radiation with carboplatin/paclitaxel or others)

A screening phase is used to determine the eligibility of a patient and may last up to 4 weeks before initiation of treatment. Eligibility and the geriatric status of potential patients will be assessed using the G8 screening tool and the Deficit Accumulation Frailty Index (DAFI). Patients are recruited independent of their PD-1 or PD-L1 expression status.

The dosing rationale for the study is based on Kudo et al. [9] and Hellmann et al. [11]. The treatment phase begins with 2nd-line nivolumab monotherapy safety run-in (240 mg fixed dose Q2W). Based on reports by Kähler et al., [14, 15] a safety assessment will be performed after 3 cycles of nivolumab monotherapy (6 weeks), during which the investigator will decide if a patient is eligible to receive nivolumab/ipilimumab combination therapy (Nivo 240 mg fixed dose Q2W; ipilimumab 1 mg/kg Q6W; arm A) or continues nivolumab monotherapy (240 mg fixed dose Q2W; arm B). This safety assessment was added due to the substantial comorbidities in most ESCC patients which may increase adverse events as compared to patients with other carcinomas and which might e.g. counteract treatment escalation. Only those patients with toxicities grade ≤ 2 will be escalated. In both arms, treatment continues until progressive disease or intolerable toxicity or withdrawal of consent or death. After another 3 cycles of treatment in both arms (approx.12 weeks from first dose) a restaging examination by radiologic imaging will be performed, which is repeated every four treatment cycles thereafter. Treatment within the context of the study is limited to 2 years.

Samples for translational research are gathered at different time points, i.e. screening/baseline (no therapy), safety assessment (after 3 cycles of nivolumab monotherapy) and restaging (after 3 cycles in treatment arm A or arm B). The study design is illustrated in Fig. 1.

**Fig. 1 Fig1:**
[figure not shown]
Study scheme. Patients may be escalated to nivolumab/ipilimumab combination therapy after a 3 cycle nivolumab-only run-in phase and positive safety assessment. GA: geriatric assessment (G8 / DAFI). ***: treatment escalation according to safety assessment results (please see full protocol). **: Chemotherapy (+/− radiotherapy) (e.g. CROSS, FLOT or similar protocols) OR any palliative systemic chemotherapy. * Stage 4 OR stage 3 non-responder to radio-chemotherapy OR any relapse after chemo-radiation OR any relapse after surgery if patient is ineligible or intolerant to standard frontline therapy OR refuses other treatment. PD1: off study despite post-progression ipi/nivo in case of toxicity and/or clinical deterioration. PD2: off study if confirmed progression according to Recist criteria V 1.1 or non-response according to immune-related response criteria. Ipilimumab 1 mg/kg IV Q6W. Nivolumab 240 mg IV Q2W. Restaging (incl. Endoscopic biopsies +PD-L1 staining)

### Study objectives

The primary objective of this trial is to demonstrate a significant survival benefit of the combination therapy with nivolumab/ipilimumab treatment in advanced ESCC compared to historical data of standard chemotherapy regimens [4].

Secondary objectives:

Tolerability of nivolumab as single agent and in combination with ipilimumab will be investigated in terms of QoL. Hence, a key secondary endpoint ‘time to QoL deterioration’ will be implemented.

Further secondary objectives are the assessment of additional efficacy and safety parameters of an intensified immunotherapy regimen and the assessment and exploration of the predictive value of structured geriatric assessments for treatment-emergent toxicities and treatment discontinuation.

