### Primary and secondary end points

#### Primary endpoint

Overall survival

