### Statistical analysis and sample size

It is hypothesized that nivolumab and ipilimumab will increase overall survival. It is assumed that an immunotherapy approach consisting of a nivolumab monotherapy in conjunction with a safety guided treatment escalation to a nivolumab/ipilimumab combination regimen increases the 1-year overall survival rate by a margin of 13% compared to historical control for standard chemotherapy (i.e. nivolumab monotherapy followed by a conditional nivolumab + ipilimumab therapy 1-yr-OS = 30% vs CTx-control 1-yr-OS = 17%) [4]. Based on these assumptions, and an exponential shape of the survival curve, a one-sided, one-sample log rank test calculated from a sample of 69 subjects achieves 90.3% power at an alpha = 0.05 one-sided significance level to detect a proportion surviving of 0.3 in the experimental group when the proportion surviving in the historic control group is 0.17. These proportions surviving are for a period of 12 month (1-year-OS rate). Subjects are accrued for a period of 12 month. Follow-up continues for a period of 24 month after the last subject is added. The probability that a subject experiences an event during the study is 0.9477. The expected number of events during the study is 65. To compensate for uninformative drop-outs a total of *N* = 75 subjects need to be recruited. All patients, both on monotherapy and on combination therapy, are subject to statistical ITT analysis.

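### The primary objective names the nivolumab/ipilimumab combination, but the only primary test evaluates nivolumab with conditional escalation in all patients, so a positive result supports the strategy and not the combination

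*Protocol article*

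**What the plan says.** **Objective.** Under Study objectives, the aim is "to demonstrate a significant survival benefit of the combination therapy with nivolumab/ipilimumab treatment in advanced ESCC compared to historical data". The abstract and the last paragraph of the Background point the same way, less explicitly.

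**Treatment.** Study design starts every patient on nivolumab alone. After three cycles the investigator decides whether the patient moves to the combination (arm A) or stays on nivolumab (arm B). Escalation depends on toxicity during the run-in and, under Safety assessment, on cardiac findings and the investigator's view of likely benefit. The abstract says eligible patients are escalated "while the other patients will remain on nivolumab only". No expected share of escalated patients is given.

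**Test.** The primary endpoint is "Overall survival". The sample-size section assumes an effect for "nivolumab monotherapy in conjunction with a safety guided treatment escalation to a nivolumab/ipilimumab combination regimen", stated as "nivolumab monotherapy followed by a conditional nivolumab + ipilimumab therapy 1-yr-OS = 30% vs CTx-control 1-yr-OS = 17"%. It plans a "one-sample log rank test calculated from a sample of 69 subjects achieves 90.3% power at an alpha = 0.05 one-sided significance level". On the population it says: "All patients, both on monotherapy and on combination therapy, are subject to statistical ITT analysis".

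**The concern.** The objective and the test name different treatments. Study design uses combination therapy as the name for what arm A receives, in contrast to monotherapy in arm B, and the secondary objectives also separate nivolumab as a single agent from nivolumab with ipilimumab. The term is therefore hard to read as shorthand for the whole regimen. The primary test pools arm A, arm B and everyone who dies or stops before the decision, and no primary contrast isolates patients who received ipilimumab.

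At stake is what a positive trial may claim. With the objective as worded, rejecting the null would be read as a demonstrated survival benefit of the combination. The pooled test can reject even when patients who received the combination did no better than the historical control.

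**Working it through.** **1. The plan's figures, and which treatment they belong to**

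Inputs from the sample-size section: one-year survival 17% (control) and 30% (strategy), exponential curves, n = 69, one-sided alpha 0.05. Timing: "Subjects are accrued for a period of 12 month. Follow-up continues for a period of 24 month after the last subject is added".

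- Monthly hazards: h0 = −ln(0.17)/12 = 0.1477; h1 = −ln(0.30)/12 = 0.1003; ratio 0.679.
- Event probability: 1 − (e^(−24·h1) − e^(−36·h1))/(12·h1) = 0.9477. Events: 69 × 0.9477 = 65.4.
- Per patient under the alternative, observed events average v1 = 0.9477. Events expected under the control hazard average v0 = v1 × h0/h1 = 1.3947. The exact variance of observed minus expected is 1.8536 (SD 1.361).
- Power = Φ{[√69 × (1.3947 − 0.9477) − 1.645 × √1.3947] / 1.361} = Φ{(3.714 − 1.943)/1.361} = Φ(1.30) = 0.903.

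The stated 90.3%, 0.9477 and 65 are reproduced, and 69/(1 − 0.08) = 75 matches the recruitment target at an implied 8% drop-out. All these figures belong to the strategy: the 30% is assumed for every enrolled patient.

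**2. Patients in the test who cannot have received ipilimumab**

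Study design puts the decision at 6 weeks = 1.38 months.

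- At the strategy's 30%: 1 − e^(−0.1003 × 1.38) = 12.9% dead by then.
- At the control's 17%: 1 − e^(−0.1477 × 1.38) = 18.4%.

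Arm B and early stoppers come on top, in unknown number. The Safety assessment section and the Discussion give 3 weeks for the same run-in, and these passages must be reconciled. At 3 weeks (0.69 months) the two figures would be 6.7% and 9.7%. Either way the share is not zero.

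**3. Can the pooled test reject when escalated patients gain nothing?**

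Assumptions:

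- A share s of patients is treated with nivolumab alone and has the 10.8-month median that the Background cites for nivolumab monotherapy (hm = ln 2/10.8 = 0.0642 per month; 46% alive at one year).
- All others have the 17% control curve.
- The values of s are assumed, since the article gives none.

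Expected counts for s = 30%, n = 69:

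- Monotherapy share, 20.7 patients: event probability 1 − (e^(−24·hm) − e^(−36·hm))/(12·hm) = 0.851, so 17.6 observed. Expected under control: 0.851 × 0.1477/0.0642 = 1.957 each, so 40.5.
- Others, 48.3 patients: event probability 0.9865, so 47.6 observed and 47.6 expected.
- Total: 65.2 observed against 88.1 expected. Z ≈ (65.2 − 88.1)/√88.1 = −2.44, beyond the critical value −1.645. The whole deficit comes from patients who never had ipilimumab.

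Simulated rejection rates for the one-sample log-rank test, each patient assigned at random with probability s, censoring uniform between 24 and 36 months:

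| Monotherapy share s | n = 69 | n = 75 |
|---|---|---|
| 20% | 50% | 53% |
| 30% | 76% | 79% |
| 40% | 91% | 93% |

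For calibration, at n = 69 the same simulation rejects in about 4% of trials when everyone follows the control curve and in 92% when everyone has 30% one-year survival.

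The scenario is deliberately simple. Survival is drawn from enrolment for everyone, and 10.8 months may be optimistic for patients judged unfit to escalate. It shows what the test can and cannot distinguish; it is not a forecast.

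**The case against.** The sample-size section already defines the intervention, effect, test and population, and its numbers are consistent for that strategy. The abstract tells readers that some patients stay on nivolumab. On this view the problem is one of wording. That much stands: nothing in the test, the sample size or the power needs to change.

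Four stronger readings are tempting but not supported.

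- **That the primary analysis is biased by patients having to survive to escalation.** Testing arm A alone from first dose against the 17% curve would be biased in that way. The article plans no such test, and pooling all patients avoids the bias.
- **That the flaw is the failure to separate ipilimumab from nivolumab.** The objective compares with historical chemotherapy, not with nivolumab. Even if all patients received both drugs from day 1, a single-arm trial could not separate them. What is specific here is that patients who never receive ipilimumab enter the test of a combination objective.
- **That the article already commits to a wrong conclusion.** It does not. The Discussion and Conclusion speak of checkpoint inhibition in general. The risk lies in the objective's wording.
- **That arm-specific analyses are missing.** Their handling belongs in an analysis plan, which is not shown.

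None of this removes the mismatch. The objective is where readers take the claim from, and it names a treatment that part of the tested population does not receive.

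**Conclusion.** The point holds as a contradiction between the stated primary objective and the primary test. A significant result would support nivolumab with safety-guided escalation against historical chemotherapy. It would not demonstrate a benefit of the combination.

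The early-death share of 13% to 18% rests only on the plan's exponential curves and the 6-week assessment. The rejection rates of roughly 50% to 93% also rest on assumed monotherapy shares of 20% to 40%, the cited 10.8-month median for those patients, and control survival for the rest. They illustrate that the test can reject without any benefit in escalated patients; they do not estimate how likely that is. The pooled intention-to-treat test is valid for the strategy, so the defect lies in the objective and in the claim it would license.

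**What to change.** Keep the pooled intention-to-treat test, the 69 evaluable and 75 recruited patients, and the 90.3% power.

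- In the abstract and under Study objectives, restate the primary objective along these lines: to show that overall survival under nivolumab with safety-guided escalation to nivolumab/ipilimumab, in all enrolled patients, is better than under historical chemotherapy with a one-year rate of 17%.
- Add one sentence saying that the primary test supports no efficacy claim specific to the combination.

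This changes text only; conduct, sample size and power are untouched. The downside is a narrower claim: the trial can speak for the strategy as a whole and not for the combination.

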### Measurements

For patient screening, the G8 screening tool and the Deficit Accumulation Frailty Index (DAFI) will be used. Patients with G8 score > 14 will be stratified as non-frail and can be directly included into to study (GoGo). If G8 scores ≤14 (frail), the DAFI questionnaire needs to be performed. DAFI-indices between 0.2 and 0.35 qualify patients as SlowGo enabling the PI to decide whether a patient is eligible or cannot participate. DAFI index ≥0.35 is defined as exclusion criterion.

In terms of safety, the screening includes an intensified assessment of cardiac co-morbidities using echocardiogram and measurement of cardiac enzymes (e.g. troponin-I). QoL will be assessed by the EORTC questionnaires QLQ-C30 and ELD14.

### Safety assessment

Procedures to be conducted during the treatment phase of the study include a safety assessment after 3 weeks (3 cycles) of nivolumab monotherapy. A study subject is eligible to escalate to nivolumab/ipilimumab combination therapy if I) the study subject has sufficient cardiac functional reserve determined by cardiac echo (less than 10% decline in ejection fraction compared to baseline assessment), II) no clinically significant abnormal troponin or ECG and III) the study subject is potentially benefitting from treatment escalation according to the judgment of the investigator.

### End of treatment

All subjects will be followed for survival until the end of the study, regardless of further treatments, or until the sponsor ends the study (follow-up extension phase).

The following procedures will be performed during follow-up every 6 weeks for the first year of follow-up, and every 8–12 weeks thereafter:assessment of survival statusrecording of all anti-cancer treatmentsrecording of all AEs and SAEs for 100 days after last dosing

### Primary and secondary end points

#### Primary endpoint

Overall survival

#### Secondary endpoints

Key secondary endpoint:Time to QoL deterioration defined as a loss of ≥10 points in the EORTC QLQ-C30 compared to base-line

Additional secondary endpoints:PFSORR according to RECIST 1.1 and immune related response criteria (modified RECIST)Duration of Response (DOR)Duration of treatmentcumulative dose intensityQoL (EORTC QLQC30 and ELD14)AEs/SAEs, toxicities according to CTC criteria v4.0Geriatric assessments:Evaluation of the predictive value of the GA containing tests (DAFI, G8-Questionaire etc.) for the occurrence of ≥ grade 3 toxicitiesPredictive value of the assessed geriatric tests for treatment discontinuationTranslational research at different time points (screening, safety assessment and first restaging)PD-1-PD-L1 expression in tumor tissue before and during treatmentpredictive biomarkers in tumor tissue (pre-treatment and re-biopsies) and bloodestablishment of organoid cultures from tumor tissue specimensResponse prediction by microbiome assessment

### Study setting

Patients will be recruited at 34 selected study sites in Germany including academic hospitals, community clinics and practitioner to achieve adequate participant enrolment. A list of study sites can be obtained from the corresponding author of this manuscript. Protocol modifications will be communicated to relevant parties upon ethics approval.

### Data collection

Data for this study will be recorded via eCRF by the site from the source documents according to standard operational procedures. Data are reviewed and checked for omissions, apparent errors, and values requiring further clarifications using computerized (automatic) and/or manual procedures. Accurate and reliable data collection will be assured by verification and cross–check of the eCRF against the investigator’s records by the study monitor. Data will be recorded and reported until the last subject will have completed the trial. Informed consent or assent forms including additional informed consent/assent forms for participation in the RAMONA translational research program will remain at the respective study sites. Confidentiality of personal information is protected by adherence to the European GDPR.

